**ABSTRACT Background:** Bariatric surgery is an effective treatment for obesity. However, around one in five people experience significant weight regain. In the months following surgery, loss of food as a hedonic reward, increased sensitivity to food-related cues, alcohol use and depression may translate into new obesogenic behaviours which can be targeted in therapy. Acceptance and Commitment Therapy (ACT) teaches acceptance of and defusion from thoughts and feelings which influence behaviour, and commitment to act in line with personal values. We will test whether people who have had bariatric surgery over one year ago find 10 weeks of ACT group therapy an acceptable treatment and whether a larger trial to test whether ACT can improve long-term post-operative outcomes would be feasible. **Methods:** This will be a feasibility randomised controlled trial (RCT) with participants randomised to either ACT or a Usual Care Support Group control. Participants will be recruited at 15-18 months post-surgery and compared at baseline, 3, 6 and 12 months. The trial will provide information about recruitment and characteristics of the proposed outcome measures to inform a definitive RCT. **Conclusions:** Trials big enough to determine whether a treatment approach works are costly, so this small study will help determine whether the methods used, such as how people are recruited, allocated to groups, and how data are collected, are likely to work on a bigger scale. This project is the first step in testing whether ACT can help people who have had bariatric surgery. **Trial Registration:** Researchregistry.com, UIN: 3959 (date registered: 10 April 2018); ISRCTN registry ID: ISRCTN52074801.

## INTRODUCTION

Worldwide, 39% of adults aged 18 years and over are overweight (BMI>25 kg/m^2), and 13% are obese (BMI> 30 kg/m^2). In the UK alone, obesity prevalence rises to 26% and related healthcare costs are £5 to £7 billion per year. Bariatric surgery is an effective treatment for obesity and its comorbidities in the long term; however, up to 20% of patients have significant weight regain which can result in further bariatric procedures, at a cost of £10,000 per re-operation, as well as the return of co-morbidities, such as diabetes. Improvements in psychological health post-surgery may also be short-lived and a particular threat to quality of life is the emergence of addictive behaviours such as alcohol dependency, which can occur in as many as nine percent of patients. This has been explained in terms of ‘addiction transfer’, that is from food to other substances post-operatively, given that food is commonly used for emotional regulation, and this function of eating is largely lost after bariatric surgery. The increased alcohol intake also contributes to post-surgery weight gain.

A number of guidelines suggest that bariatric surgery should be undertaken in the context of a multidisciplinary team that can provide psychological support, though the type of support is not specified. Limited benefit has been found for behavioural interventions which promote healthy lifestyle changes. For instance, a systematic review of 11 trials found small improvements in weight loss at 12 months post-bariatric surgery; however, the included trials were poor quality, short-term and there were few data on outcomes important to patients, such as quality of life. Understanding of the mechanism of action of interventions is also limited. Proposed intervention targets include: loss of food as hedonic reward, emotional regulation, disordered eating, distress intolerance, increased sensitivity to food-related cues, reduced physical activity, alcohol use, and depression. Mindfulness-based or ‘third wave’ cognitive behaviour therapy approaches such as Acceptance and Commitment therapy (ACT) target these mechanisms and have previously demonstrated effectiveness for weight loss in the general population.

In bariatric surgery populations, a small trial (n=39) has demonstrated improvements in an ACT group relative to treatment as usual in areas such as disordered eating, body dissatisfaction, quality of life and acceptance for weight-related thoughts and feelings. Mean time post-surgery in this cohort was 15.5 (range: 4–38) months; however, the optimal timing for psychological intervention is unknown. An RCT (n=162) of a health psychology intervention, which addressed psychological issues such as dietary control, self-esteem, coping and emotional eating, and which was delivered two weeks pre-operatively prior to discharge from hospital, and 3 months post-operatively, had no impact on weight loss at 12 months. Intervention at a later stage may therefore be more beneficial. This makes intuitive sense if it is considered that many of the mechanisms proposed to contribute to weight gain, for example loss of food as a hedonic reward, increased sensitivity to food-related cues, alcohol use, depression, develop post-surgery and may take time to translate into new obesogenic behaviours which can be targeted in therapy. Several studies have found that 20-30% of patients regain some weight within the first 24 months post-surgery; ironically, it is at this stage when patients may be discharged from follow up clinics.

This feasibility RCT was therefore designed to determine whether ACT, delivered 15-18 months post-bariatric surgery (that is when patients are approaching discharge from secondary care), is acceptable to patients, and to determine the methods of a future, larger trial of effectiveness.

## **METHODS**

### ***Design***

This will be a feasibility study for a single-centre, parallel group, single blind, two arm trial, with participants randomised to either 10 weeks of ACT group therapy or a Usual Care Support Group control. The trial has received a favourable ethical opinion from London-Westminster REC (18/LO/1256).

### ***Setting***

The trial will be conducted with adult ( $\geq 18$  years old) patients from a London-based weight management centre.

### ***Participants and recruitment***

#### ***Inclusion criteria***

Adults of any sex (aged  $\geq 18$ ), who have undergone any bariatric-surgery (i.e., gastric bypass, sleeve gastrectomy, gastric band and re-operations), patients more than one year out of surgery and who are willing and able to give informed consent for participation in the study.

#### ***Exclusion criteria***

Suicidal ideation (score of  $>0$  on Question 9, PHQ-9). Patients who are unable to communicate in English as the intervention is delivered in English and unable to commit to attendance to 10 sessions.

Potentially eligible participants will be provided with a Participant Information Sheet (PIS) and a PHQ-9 to screen for suicidal ideation by a clinician at their regular follow-up appointment. Patients who do not attend will be posted the PIS with their routine appointment reminder letter to avoid selection-bias.

Eligible patients attending the clinic for their routine follow up appointment, who verbally express an interest in participating in the study will be approached by a researcher after their appointment and invited to read through the PIS. They will have the opportunity to ask questions about the study and, if the patient wishes to participate, an appointment will be made with the researcher to obtain written consent, and for baseline data collection and randomisation.

### ***Randomisation***

Participants who meet the eligibility criteria will be randomised to either ACT or the Usual Care Support Group. Randomisation will be conducted by a researcher, independent of the trial, running R program scripts. The randomisation method uses permuted blocks of variable size, randomly varying from two to six participants. All eligibility criteria will be checked before randomisation by the researcher who will then request randomisation. Each patient will be given a unique patient study number which will be sent to the independent researcher running the R program randomisation script. The program generates a randomised patient study number assigning them to either the ACT or the Usual Care Support Group. This is emailed back to the study clinician (SS) who then informs the participant of their allocation and provides details of where and when to attend. Equal number are allocated to each condition. The flow of participants through the study is depicted in Figure 1.

[figure not shown]

**Figure 1: Participants through the study.**

### **Blinding**

In a randomised comparison of this type, patient blinding is clearly impossible. The researcher (LC) will however be blind to randomisation status and will be asked to give their opinion on randomisation status to determine whether blinding is adequate.

### **Sample size**

As this is a feasibility study and no hypothesis testing will occur, a power calculation has not been conducted. Sample sizes between 24 and 50 have been recommended for feasibility studies, however to allow for loss to follow up, estimated at 30%, we will aim to recruit 58 participants. Loss to follow up and intervention and Usual Care Support Group attrition, including reasons, will be recorded to inform power calculations for a definitive RCT. This information will be recorded in a consort diagram.

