### **Intervention**

#### **ACT group therapy**

Ten 90-minute sessions will be delivered weekly by a clinical psychologist trained in bariatric psychological support and ACT. Components of the intervention are shown in Table 1. The ACT intervention has been adapted from a manual used in a previous pilot trial for bariatric surgery patients who experienced weight regain. The following adaptations were made by ACT trained members of the research team (EB, DLB) and agreed with the multidisciplinary team and service user advisors: (1) Reduced emphasis on eating behaviours and increased emphasis on living in line with personal values. For instance, the necessity for daily weigh-ins, calorie counting, and food recording for all participants has been removed. Instead, participants are encouraged to set personalised, achievable goals (which may or may not involve specific eating behaviours) which move them towards their self-defined values. The manual includes support to enhance values clarity. (2) A stance of self-compassion is actively encouraged throughout the intervention.

The intervention focuses on fostering key ACT processes, including acceptance of difficult internal processes (e.g., thoughts, feelings, urges), defusion from thoughts, values clarification, willingness and committed action, self as context and linking values to present moment decision-making. The aim is to enhance participants’ ability to adhere to the restrictive postoperative diet in order to prevent weight regain whilst maintaining or improving quality of life.

As part of the intervention, each week participants complete two measures of ACT processes: The Bullseye (adapted from Lundgren’s Bullseye Worksheet (2012)) which facilitates values clarification and prompts them to consider how closely they are living in line with their values, and the CompACT: a brief measure of ACT processes designed for clinical and research use. The intervention also includes standard psychoeducation and behavioural interventions for weight management post-bariatric surgery. Homework is set and reviewed weekly to reinforce in-session learning. In addition, and at the therapist’s discretion, participants are alerted to reinforcing resources such as ACT-relevant ‘YouTube’ videos.

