**Data collection and measures**

A standardised battery of measures will be completed at baseline, three, six and 12 month follow up, except for weight and the King’s Obesity Staging Criteria which will be collected at baseline and 12 month follow up only to allow for meaningful change. Demographic data: self-reported medical history, age, gender, work status, educational level, ethnicity, marital status, number of dependents, current or past psychological therapy and current medications, will also be collected at baseline. Baseline and 12 month follow up data will be collected face to face to coincide with routine clinic appointments; three and six month follow up data will be collected via telephone.

*Primary outcome measures*

The primary outcome is the feasibility of the trial methodology. This will be measured by, (1) The willingness of participants to be randomised, measured by recording the number of participants who drop out of the study after they have been randomised, (2) the number of eligible patients attending clinic, as assessed by calculating the percentage of patients who meet eligibility criteria at screening, (3) follow-up rates, assessed by the percentage of participants retained until 12 month follow-up and providing complete datasets, (4) adherence to the intervention or control, assessed by number of sessions attended, (5) reasons for attrition, (6) the time needed to collect data and (7) the acceptability of the intervention at 12 month follow-up, as assessed by a 5 point likert scale (1=“Not at all”, 3=“somewhat”, 5=“Very”) to evaluate how helpful participants found the treatment, their satisfaction with it, and how likely they would be to recommend it to a friend and (8) the standard deviation of weight maintenance (<5% weight gain from baseline assessment) or weight loss, in order to estimate the required sample size for a future trial (measured at study close-out).

*Secondary outcome measures*

Outcomes relating to (A) obesity, health and wellbeing, (B) costs, and (C) measures of ACT processes will be collected to test the appropriateness and acceptability of measurement instruments to be used as outcomes in a full trial. The validated instruments to be used are listed below.

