#### *Statistical data analysis*

Analyses will be undertaken using R program. All significance tests will be 2-tailed and alpha will be set at  $p < 0.05$ . The distribution of the study population will be characterised using descriptive summary statistic parameters, that is median, range, mean, and standard deviation. Then, we propose to use ANCOVA to calculate variations within primary and secondary outcome measures pre-treatment and at follow-up. Anonymised data from those who decline to participate will also be reported. Complete case analysis and intent-to-treat analyses (using last measurement carried forward for participants who provided baseline assessment measurements) will be conducted.

A cost-consequence analysis (CCA) will be carried out from a National Health Service (NHS) perspective. This involves listing the costs and outcomes associated with ACT and the Usual Care Support Group separately, allowing decision-makers to compare the relative value of approaches, and by calculating resource use. The intervention costs will be calculated based on the activities involved in delivering the programme such as staff salaries, administrative and managerial costs.

Total costs of the individuals in the two groups will be compared and estimated by multiplying the resource use with the unit costs of health and social care. We will present the additional costs associated with the intervention and present the costs alongside the benefits (if any) identified in the trial. Sensitivity analyses to model uncertainties around all key cost and outcome parameters, and plausible ranges will be specified using information from the trial and from the literature specific to the population in the study will be conducted.

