## **DISCUSSION**

This study aims to establish the feasibility of conducting a larger scale RCT to examine the impact of ACT on bariatric patients 15-18 months post-surgery. Previous small-scale studies of acceptance-based behavioural intervention for post-operative populations have found benefits in favour of ACT compared with usual care. The different studies focused on different outcomes, but benefits identified included reduced cravings and sweet consumption, reduced disordered eating and improved body dissatisfaction and quality of life, as well as weight loss (a clinically significant average of 6 kg or 5% weight loss in treatment completers,  $n=23$ ). Enhanced psychological flexibility, a core ACT process, was identified as one mediator for benefits in one trial, though other processes have also been proposed as important. This study will therefore examine a wide range of potential treatment outcomes and will test for possible mediators and moderators of effect. In the earlier studies, the time since surgery varied widely between participants. The current study will focus on patients who have reached a critical stage in their treatment; a stage which has been identified as high risk for weight regain and at which point they are currently discharged from services.

Despite the potential benefit of psychological intervention and recommendations within various guidelines that it should be offered to bariatric patients, psychological support is not provided as part of routine post-operative care. Such support could potentially reduce the high costs to the patient and to society of weight regain, re-operations and the return of physical and psychological co-morbidities post bariatric surgery. This feasibility trial is the first step in helping to determine whether ACT group therapy is acceptable to post-bariatric surgery patients, and will provide insight into the optimal methods to employ for a future randomised controlled trial to determine its effectiveness.

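### The protocol rules out hypothesis testing, then sets two-sided tests at 0.05, and it applies ANCOVA to primary feasibility outcomes, seven of whose eight components have no pre-treatment value

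*Protocol*

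**What the plan says.** Three places in the protocol bear on testing.

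- Sample size: "As this is a feasibility study and no hypothesis testing will occur, a power calculation has not been conducted". The absence of testing is the reason given for having no power calculation.
- Statistical data analysis: "All significance tests will be 2-tailed and alpha will be set at" p < 0.05. Nothing there calls the tests exploratory.
- Discussion: the study "will test for possible mediators and moderators of effect".

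Two places bear on the method for the primary outcome.

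- Data collection and measures: "The primary outcome is the feasibility of the trial methodology", followed by eight numbered components. The first, willingness to be randomised, is "measured by recording the number of participants who drop out of the study after they have been randomised".
- Statistical data analysis: after a descriptive step, "we propose to use ANCOVA to calculate variations within primary and secondary outcome measures pre-treatment and at follow-up". The descriptive step reads: "The distribution of the study population will be characterised using descriptive summary statistic parameters, that is median, range, mean, and standard deviation".

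**The concern.** The reason for having no power calculation fails if the analysis section is followed. A study of this size would then produce p-values against a 0.05 threshold on many instruments, with no multiplicity control and no effect size that it was designed to detect. A chance significant result could be read as a signal of efficacy, and a non-significant one as evidence of no effect. Either could distort the decision on a definitive trial.

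Separately, the only model named for the primary outcome does not suit most of it. ANCOVA of a follow-up value on its pre-treatment value needs the same numeric quantity on each participant at both times, plus an arm to compare. Most feasibility measures have no such pair of values.

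**Working it through.** **1. The statements on testing.** Sample size says that no tests will be done. Statistical data analysis gives their sidedness and alpha, and the Discussion names further tests. No sentence in the protocol limits the first statement to the primary outcome or marks the later tests as exploratory.

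**2. The eight primary components against ANCOVA.**

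| Component | Type | Pre-treatment value? |
|---|---|---|
| 1 Drop-out after randomisation | count | no |
| 2 Eligibility at screening | percentage, fixed before any arm exists | no |
| 3 Retention to 12 months with complete data | percentage | no |
| 4 Sessions attended | count | no |
| 5 Reasons for attrition | categories or text | no |
| 6 Data-collection time | duration | no |
| 7 Acceptability at 12 months | 5-point rating | no |
| 8 SD of weight maintenance or loss | summary statistic | weight itself: yes (baseline and 12 months) |

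The model fails for components 1 to 7. For component 8 it could be fitted to weight, although the component itself is an SD to be estimated, not a contrast between arms.

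**3. The sample size.** The protocol gives a recommended range of 24 to 50, 30% loss and a target of 58. Inflating by N/(1 − 0.30), rounded up: 24 gives 35, 40 gives 58 and 50 gives 72. So 58 fits an assumed 40 completers. In the other direction, 58 × 0.70 = 40.6, or about 20 per arm. The target is consistent with the text and is not in dispute.

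**4. False positives if the tests were run.** The protocol lists 15 secondary instruments: 7 on obesity, health and wellbeing, 3 on costs and 5 on ACT processes. Thirteen are taken at three follow-ups; weight and the King's criteria are taken at 12 months only. The chance of at least one false positive in k independent tests is 1 − 0.95^k, and the expected number is 0.05k.

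- One test per instrument: k = 15, 1 − 0.95^15 = 0.537, expected 0.75.
- One test per instrument and visit: k = 13 × 3 + 2 × 1 = 41, 1 − 0.95^41 = 0.878, expected 2.05.

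Independence is an assumption, and outcomes on the same participants are correlated. The protocol does not fix k: subscale tests would raise it, and leaving out the resource-use inventory, which goes to the cost-consequence analysis, would lower the first case to 14 (0.512).

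**5. Power.** Two-sample t-test, two-sided 0.05, equal arms. The 0.5 SD effect is an assumption, since the protocol gives none. With baseline correlation r (also an assumption), ANCOVA is approximated by dividing the effect by √(1 − r²): 0.5/√0.75 = 0.577 for r = 0.5, and 0.5/√0.51 = 0.700 for r = 0.7.

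| Per arm | Unadjusted power | r = 0.5 | r = 0.7 | Effect for 80% power, unadjusted | r = 0.5 to 0.7 |
|---|---|---|---|---|---|
| 20 (completers) | 0.338 | 0.43 | 0.58 | 0.91 SD | 0.79 to 0.65 SD |
| 29 (all 58) | 0.465 | 0.58 | 0.75 | 0.75 SD | 0.65 to 0.53 SD |

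The 29-per-arm row applies if carrying the last measurement forward keeps all 58 in the analysis.

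**6. What a rate would look like.** If 41 of 58 were retained (70.7%), the Wilson 95% interval is 58% to 81%.

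**The case against.** The best defence is that feasibility is the primary outcome, that efficacy is left to a definitive trial, and that the data-collection section already says how the components are to be assessed: percentages, numbers of sessions, a rating. On that view the testing and ANCOVA sentences are loose drafting. Much of this stands. All eight components can be reported as defined, without ANCOVA. It does not remove the contradiction, and an unseen SAP would not either, because the point concerns what the protocol states, not what it leaves out.

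Some stronger readings are tempting but not supported.

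- A reader might infer that the primary analysis cannot be run at all, or that the primary outcomes are all counts. Only drop-out and sessions attended are counts; weight behind component 8 has a baseline; and the failure is confined to ANCOVA on components 1 to 7.
- A reader might infer that mediation cannot be tested between arms because the CompACT is described only within the ACT sessions ("As part of the intervention, each week participants complete two measures of ACT processes"). The protocol never names the CompACT as a mediator. Five other ACT-process measures are in the battery for both arms at baseline, 3, 6 and 12 months.
- A reader might double the 41 tests because both complete-case and intention-to-treat analyses are planned. These use largely the same data on the same participants and are not separate families of tests.
- A reader might take 34% as the power of the plan. It is the unadjusted figure for 20 per arm; the planned model adjusts for baseline, and one planned analysis set could be larger.

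The lack of stated confidence intervals is not itself an error, since a protocol may leave interval reporting to the SAP.

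**Conclusion.** The point holds on two counts, and neither depends on a calculation. First, the protocol denies hypothesis testing, uses the denial to justify having no power calculation, and then plans tests at 0.05 together with mediator and moderator tests. Second, it applies ANCOVA from pre-treatment to follow-up to a primary outcome of which seven of eight components have no pre-treatment value, one of them being settled before randomisation.

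The figures show what is at stake and are illustrative. The chance of at least one false positive runs from about 54% to 88% over 15 to 41 tests, if these are independent. Power at an assumed 0.5 SD is about 34% to 46% unadjusted, and about 43% to 75% for assumed baseline correlations of 0.5 to 0.7. The text is wrong as written and should be corrected before analysis, because following it would yield significance claims that the protocol itself disclaims.

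**What to change.** - Bring Sample size, Statistical data analysis and Discussion into line. Either remove the sentence on significance tests and alpha, or keep the tests and the mediator and moderator analyses but label them all exploratory and not for efficacy inference. If tests are kept, amend the Sample size statement to match.
- Report components 1 to 7 descriptively, as counts, proportions or summaries suited to each, with 95% confidence intervals for rates. Report component 8 as the estimated SD with its confidence interval.
- Limit ANCOVA to continuous outcomes with a baseline value, reported as baseline-adjusted differences between arms with 95% confidence intervals.

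The cost is wording only. Recruitment of 58, the visit schedule and the instruments do not change. The sponsor gives up, or relabels, p-values that the Sample size section says it does not need.
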